## Abstract

**Background:**

Australia persistently has one of the highest rates of colorectal cancer (CRC) in the world. Australia’s National Bowel Cancer Screening Program (NBCSP) sends a biennial Faecal Immunochemical Test (FIT)—the ‘NBCSP kit’—to everyone eligible for the programme between 50 and 74 years old; however, participation in the programme is low, especially in the 50- to 60-year-old age group. Our previous efficacy trial (‘SMARTscreen’) demonstrated an absolute increase in uptake of 16.5% (95% confidence interval = 2.02–30.9%) for people sent an SMS with motivational and instructional videos, from their general practice prior to receiving their NBCSP kit, compared to those receiving usual care. Building on the strengths of the SMARTscreen trial and addressing limitations, the ‘SMARTERscreen’ trial will test the effect on participation in the NBCSP of sending either an SMS only or an SMS with online video material to general practice patients due to receive their NBCSP compared to ‘usual care’.

**Methods:**

SMARTERscreen is a three-arm stratified cluster randomised controlled trial involving 63 general practices in two states in Australia. Eligible patients are patients who are aged 49–60 years and due to receive their NBCSP kit within the next 2 weeks during the intervention period. General practices will be equally randomised to three trial arms (21:21:21, estimated average 260 patients/practice). The two interventions include (i) an SMS with an encouraging message from their general practice or (ii) the same SMS with weblinks to additional motivational and instructional videos. The control arm will receive ‘usual care’. Using the intention-to-treat approach, primary analysis will estimate the three pair-wise between-arm differences in the proportion of eligible patients who participate in the NBCSP within 6 months of when their kit is sent, utilising screening data from the Australian National Cancer Screening Register (NCSR). Patient intervention adherence to the interventions will also be evaluated. Findings will be incorporated into the Policy1-Bowel microsimulation model to estimate the long-term health benefits and cost-effectiveness of the interventions.

**Discussion:**

SMARTERscreen will provide high-level evidence determining whether an SMS or an SMS with web-based material sent to general practice patients prior to receiving their NBCSP kit increases participation in bowel cancer screening.

**Trial registration:**

Australian New Zealand Clinical Trials Registry ACTRN12623000036617. Registered on 13 January 2023.

Trial URL: https://www.anzctr.org.au/Trial/Registration/TrialReview.aspx?id=385119&isClinicalTrial=False

## Introduction

### Background and rationale {6a}

Australia has one of the highest rates of colorectal cancer (CRC) in the world [1]. Currently, 40% of CRC cases are diagnosed at stage 3 or 4 leading to a poorer prognosis [2]. Screening for precancerous adenomas and early-stage cancer, at which time they can be easily treated, improves outcomes and is cost-effective [3, 4]. Australia has a National Bowel Cancer Screening Program (NBCSP), which is a coordinated, population-based screening programme that sends immunochemical Faecal Occult Blood Test (FIT) kits to eligible Australians aged 50 to 74 years every 2 years. The kits are free and sent directly to a person’s home where two samples can be self-collected and returned for testing [5]. Despite the convenience of this process, uptake of the NBCSP is only 40.9% with fewer people in the younger age groups completing the kit; currently, only 31.6% of people between 50 and 54 years return the kit for testing [6]. Modelling has estimated that if screening participation increased by an additional 10%, 24,300 additional CRC diagnoses and 16,800 additional CRC deaths could be prevented, and an additional $300 million dollars in healthcare expenditure saved over the next 25 years in the Australian population [7].

Multiple strategies have been tested to increase CRC screening uptake, all having varying degrees of success either as single or multifaceted interventions [8]. Of these, endorsement from a patient’s general practitioner (GP) has been demonstrated to have one of the biggest impacts on increasing uptake [9, 10]. Direct engagement by GPs with their patients increases patient awareness about screening and reduces anxiety and fear about participating in screening [11]. In Australia, the kit is sent directly to the participant from the NBCSP, and currently, there is no coordinated and efficient way for the GP to prompt or encourage their patients to participate in screening.

Short message services (SMS) are being used more often by general practice to communicate with patients because this approach provides an opportunity to reach large numbers of patients in real time and messages can be viewed discreetly multiple times at an individual’s convenience and have demonstrated success at increasing screening uptake internationally[12, 13]. Between 2020 and 2021, we undertook a trial in 21 general practices, called SMARTscreen to test an intervention which combined, in one SMS, multiple evidence-based components known to increase screening uptake including a message of endorsement from a credible source (i.e. the GP) and weblinks to motivational video narratives and instructions for how to do the test [14]. The SMS was sent to patients from their general practice just before they were due to receive their NBCSP kit. The SMARTscreen trial demonstrated that sending SMS prompts from a patient’s general practice increased NBCSP kit return by 16.5% (95% confidence interval = 2.0–30.9%; 39% kit return in the intervention practice compared with 23% in control practices) [15] and was acceptable and feasible to both practice staff and patients (in submission). Generalisability of the results was limited because only one regional location in Australia was involved and, as the data were collected at the aggregated practice level, this meant that the analysis by individual patient characteristics was limited. We were also unable to differentiate between the effect of receiving the SMS and the contribution of the materials accessed via weblink within the SMS message (i.e. video content) [15].

Another limitation was that the date the patient’s NBCSP kit was due in the SMARTscreen trial was approximated from either birthdate or previous kit return date data recorded in general practice electronic health record (EHR). Recently, the Australian Government launched a National Cancer Screening Register (NCSR) that enables a coordinated approach to invitations, reminders, and follow-up for bowel and cervical cancer screening. The NCSR allows GPs to directly access their patients’ screening status, including when the next kit is due and their screening history through their electronic medical software [16]. Using the NCSR data will provide a more accurate date for the FIT arrival to inform the timing of SMS interventions.

The SMARTERscreen trial builds on the strengths and addresses the limitations of SMARTscreen. This trial will involve testing the effect of an SMS alone or the SMS in combination with a web-based link with revised video content, compared with usual care in a larger and more diverse general practice population across metropolitan and rural areas. The due date for when the NBCSP kit will be sent, and the outcome of screening participation will be collected directly from the NCSR records instead of relying on general practice electronic health records and therefore will provide more reliable information. Individual patient characteristics will be collected from the NCSR and practices providing more information about the impact of the interventions on screening behaviour by age, sex, previous screening history, and location (based on the geographical location of the patients’ general practice).

## Objectives {7}

SMARTERscreen is a three-arm parallel cluster randomised controlled superiority trial in general practices in the Australian states of Victoria and Queensland. The general practices will be allocated on 1:1:1 ratio to test all three pair-wise comparisons between arms:Control arm: practices continue with usual care in which general practitioners continue with opportunistic discussions about bowel cancer screening;Intervention arm 1: an ‘SMS only’ message sent to the patient from their general practice advising them that their FIT kit will be coming in the mail soon and that their GP strongly advises that they complete itIntervention arm 2: an ‘SMS bundle’ is sent which is the same message as for intervention 1, but with a weblink to extra online information and resources designed to increase participation in the NBCSP.

The trial aims to assess whether sending either an SMS alone or an SMS in combination with a web-based link to additional motivational resources to 49- to 60-year-old general practice patients who are due to receive their kit from the NBCSP will increase CRC screening uptake in the programme within 6 months of when their kit is due compared to the control arm, respectively. Further, the trial aims to assess whether including a web-based link in the SMS to motivational and instructional videos increases screening uptake compared to SMS alone. Patients’ screening status, defined as having a recorded FIT result within 6 months of when their kit is due, will be extracted at the individual level from the NCSR.

Secondary aims will be:To identify patient characteristics, including age, sex, previous screening, and location of practice, that modify the intervention effect of SMS only and SMS bundle compared to the control on proportion who uptake CRC screening within 6 monthsTo evaluate adherence to the intervention by measuring the number of SMS/SMS bundles unable to be delivered to patients relative to the number sent, the proportion of people who opt out of receiving more SMS/SMS bundles, the proportion of people who receive the SMS bundle who open the SMS weblink and view the videosTo evaluate the cost-effectiveness of the two interventions compared to usual care and potential health cost savings if a SMS intervention were to be adopted and implemented nationally. This objective includes estimating the potential number of lives saved by increasing screening uptake.

### Hypotheses

Our primary hypotheses are:A GP practice-endorsed SMS sent from general practice to patients aged between 49 and 60 years old and due for a NBCSP kit will increase the proportion of patients who return the NBCSP kit within 6 months of when their kit is sent compared to usual care;A SMS bundle with a GP endorsement of the NBCSP and additional material (i.e. motivational and instructional videos) from general practice to patients aged between 49 and 60 years old and due for a NBCSP kit will increase the proportion of patients who return the NBCSP kit within 6 months of when their kit is sent compared to usual care;Proportion of general practice patients who return the NBCSP kit within 6 months of when the kit was due will differ between patients aged between 49 and 60 years old and due for a NBCSP kit who receive SMS bundle with a GP endorsement of the NBCSP and additional material (i.e. motivational and instructional videos) compared to those who receive an SMS with only GP endorsement of the NBCSP.

Secondary hypotheses:

Sending a GP practice-endorsed SMS with/without additional motivational material to people before their kit is sent will be cost-effective compared with usual care.

## Trial design {8}

SMARTERscreen is a stratified cluster randomised controlled superiority trial in 63 general practices randomised equally into one of three arms (21:21:21), using block randomisation within four strata [Victoria vs Queensland (50% from each State), and metropolitan/larger regional vs rural/smaller regional location (60% from metropolitan/larger rural, 40% rural/smaller regional locations) of the general practice].

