#### Sample size {14}

Sample size was based on 80% power for an overall two-sided significance level of 5% (alpha), and an intraclass correlation coefficient (ICC) of 0.01. Planned primary comparisons are the two intervention arms (SMS only and SMS bundle) with the control arm, respectively, and the SMS only intervention with the SMS bundle. The Holm-Bonferroni correction was used to control the family-wise error rate across three pairwise comparisons. Thus, for the purposes of the sample size calculations, we conservatively set the alpha at 0.017. We assumed that 34% of patients in the control arm will have completed their FIT, based on the National screening data [20]. Sixty-three practices with an average of 260 of eligible patients per practice (standard deviation = 197; range 51 to 753; coefficient of variation = 0.76) [15] will be sufficient to detect a difference of 10% absolute increase in participation in the NBCSP within 6 months from when the NBCSP kit is due between each intervention arm (SMS only and SMS bundle) and control arm (44% vs 34%), respectively; and to detect a smaller difference of 7.5% (44% vs 51.5%) between the SMS only and SMS bundle intervention arms. The total of 63 practices allows for an additional practice per arm for potential loss of practices due to closures or merges. A national 10% increase in screening participation would prevent 27,000 bowel cancers and 16,800 deaths and is associated with an additional $200 million in costs over current screening levels over the next 20 years [4]. We anticipate that adding the weblinks to motivational and instructional videos in the SMS would have a smaller additional effect on increasing screening participation compared to a SMS only.

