## Assignment of interventions: allocation

### Sequence generation {16a}

The unit of randomisation will be the general practice (cluster). Once all general practices have been consented and eligible participants have been identified within practices, the eligible patient lists will be sent to the NCSR to be enriched. Once the data have been sent back to the practices, the general practices will be randomly allocated with a 1:1:1 ratio to either the control or one of the two intervention arms. Randomisation will be stratified by geographical location (metropolitan/larger regional and rural/smaller regional) and state (Queensland and Victoria), and each stratum will have a computer-generated random allocation sequence with random permuted block sizes.

General practice location will be stratified as either metropolitan/larger regional if located in MMM 1–3 and rural/smaller regional if located in MMM 4–6 [17]. If two practices that share EHR are located across the two geographic locations (MMM1-3 and MMM4-6), they will be allocated to the MMM category where the main practice is located for randomisation.

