#### The method (Fig. 4)

##### Step 1

The eligible patient list will be collected from each general practice EHR using a bespoke Structured Query Language (SQL) query. The list will be saved as a comma-separated values (.csv) file securely on the practice computer, with a name specific to the study identifier of the practice (practice ID) and the date of extraction (Dataset 1).

##### Step 2

The practice manager will add three columns of data including (1) a column with a Provider number for the principal GP for that practice, (2) a column with a unique trial ID code for each patient (e.g. GP0010001), and (3) a column with a unique practice ID code for each practice (e.g. GP001) (Dataset 2).

##### Step 3

This dataset will be saved as a.csv file and uploaded to the NCSR using a secure file transfer protocol (SFTP).

##### Step 4

Once the NCSR have the.csv file (Dataset 2), they will match the patients in the NCSR by date of birth, Medicare number, and name. The.csv file will be enriched with five additional columns of data for each person: one for the date they returned their last NBCSP kit (or blank if they have not returned one before) [‘Date_kit_returned’], one with the date their next NBCSP kit is due [‘Date_Kit_Due’], one if the NCSR cannot match patients’ identifying data with the register’s records [‘1’ if records match with NCSR database, ‘0’ if data in the.csv file does not match the register], one calculating the date the SMS will be sent [‘Date SMS is due’ which will be calculated as the (‘Date the NBCSP kit is due’ − 14 days)], and one calculating the patient’s age at the time when their kit is due [‘Age in months when kit is due’, which will be calculated as (= ‘Date the NBCSP kit is due’ − ‘Date of Birth’ in years, multiplied by 12)].

The NCSR will then save a.csv file (i.e. NCSR dataset) for every practice (Dataset 3).

##### Step 5

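### Prior screening is known before randomisation but is left out of both the allocation and the primary model, and the stated 21:21:21 split is not guaranteed by the method described

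*Protocol article*

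**What the plan says.** Trial design {8} describes 63 practices "randomised equally into one of three arms (21:21:21), using block randomisation within four strata". The strata cross state ("Victoria vs Queensland (50% from each State") with location ("60% from metropolitan/larger rural, 40% rural/smaller regional locations"). Sequence generation {16a} adds that "each stratum will have a computer-generated random allocation sequence with random permuted block sizes". The block sizes are not given, and Concealment mechanism {16b} withholds them until allocation is complete.

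On timing, Sequence generation {16a} places randomisation after the practices have agreed and their patients have been listed: "Once all general practices have been consented and eligible participants have been identified within practices". The lists go to the national register for enrichment, and allocation follows once they are returned. Step 4 of The method (Fig. 4) shows that enrichment includes prior participation: "one for the date they returned their last NBCSP kit (or blank if they have not returned one before". Practice size is the length of the list. Sample size {14} expects it to vary widely ("standard deviation = 197; range 51 to 753; coefficient of variation = 0.76").

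The primary model in Statistical methods {20a} adjusts for remoteness and state only. Methods for additional analyses {20b} adds sex, age and ever/never screened as covariates in a sensitivity analysis, and uses previous screening as a subgroup factor.

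**The concern.** There are two separate issues.

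First, the stated split and the stated method do not match. A stratum whose size is not a multiple of three cannot be divided equally among three arms, and with random block sizes the last block in a stratum may be cut short. Equal arms are then a matter of luck. Random block sizes hinder prediction when units enter one at a time. Here all practices are in hand before any is allocated, so that protection adds little.

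Second, the protocol treats prior screening as important, both as a candidate effect modifier and as a pre-specified covariate, and it holds that information before allocation. It uses it neither to balance the arms nor in the primary estimate. At stake is the precision of three pairwise contrasts in a trial of 63 clusters, where most of the variance comes from differences between practices.

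**Working it through.** **Inputs from Sample size {14}.** Mean 260 patients per practice, coefficient of variation (CV) 0.76, ICC 0.01, alpha 0.017 per comparison (0.05/3), 80% power. The hardest contrast is 44% v 51.5%. One spare practice per arm is included in the 21.

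**Reproducing the plan's figure.** Design effect = 1 + ((1 + CV²) × m − 1) × ICC = 1 + (1.5776 × 260 − 1) × 0.01 = 5.09. With k practices per arm, SE = √[(0.44 × 0.56 + 0.515 × 0.485) × 5.09 / (260k)]. With a t reference on 2(k − 1) degrees of freedom, k = 19 gives about 79% power and k = 20 about 81%. So 20 are needed, plus one spare makes 21 per arm, 63 in total. The stated figure is reproduced.

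**How often the arms come out at 21 each.** Expected stratum sizes, if the factors cross evenly, are 63 × 0.5 × 0.6 = 18.9 and 63 × 0.5 × 0.4 = 12.6. I took 19, 19, 13 and 12. Stratum counts and block sizes are assumptions. Results from 10,000 simulated allocations per row:

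| Strata | Blocks | Exactly 21:21:21 | Some arm ≤ 19 |
|---|---|---|---|
| 19/19/13/12 | fixed 3 | 22% | 0% |
| 19/19/13/12 | random 3/6 | 18% | 12% |
| 19/19/13/12 | random 3/6/9 | 15% | 23% |
| 18/18/15/12 | fixed 3 | 100% | 0% |
| 18/18/15/12 | random 3/6 | about 44% | 6% |

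Across repeated runs and neighbouring stratum counts that are also mostly not multiples of three, the two random-block settings give about 15 to 19% and 12 to 24%.

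**What this costs in power (44% v 51.5%, alpha 0.05/3).**

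| Practices | Normal reference | t reference |
|---|---|---|
| 21 v 21 | 86% | 83–84% |
| 19 v 21 | 84% | 81% |
| 18 v 21 | 83% | 80% |

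An arm of 18 or fewer occurs in about 0.6% of draws with blocks 3/6 and about 3% with 3/6/9.

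**What prior screening could buy.** The between-practice part of the design effect is 1.5776 × 260 × 0.01 = 4.10, and 4.10 / 5.09 = 81% of the variance of a between-arm difference. If a practice-level covariate has correlation r with the practice's underlying participation, adjusting for it removes about 0.81 × r² of that variance:

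- r = 0.3: 0.806 × 0.09 = 7%, worth 21 / 0.927 = 22.6 practices per arm
- r = 0.5: 0.806 × 0.25 = 20%, worth 21 / 0.799 = 26 per arm
- r = 0.7: 0.806 × 0.49 = 39%, worth 21 / 0.605 = 35 per arm

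The values of r are assumed; the protocol gives none.

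**Practice size.** With CV 0.76 and 21 practices, an arm's patient total has an SD of 0.76 / √21 = 16.6% of its mean. In simulations with lognormal practice sizes, ignoring strata, the median ratio of largest to smallest arm was 1.23 to 1.29, and it exceeded 1.5 in 7 to 18% of draws.

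**The case against.** The strongest reply is that stratified permuted blocks for 63 clusters on two factors is a standard and valid design. Objectives {7} and Sequence generation {16a} both state a 1:1:1 ratio, so 21:21:21 reads naturally as the plan rather than a guarantee. Exact balance is even certain if every stratum is a multiple of three and blocks are fixed at 3. The simulated probabilities rest on block sizes and stratum counts that the protocol does not give. All of this stands, and it reduces the allocation issue to one of wording and easy improvement.

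A reader might infer that an uneven draw uses up the spare practice and leaves the trial underpowered. The figures do not support that: the total stays at 63, and power holds at about 80% or more even at 18 v 21.

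A reader might also set the chance difference between practices against the 7.5-point contrast. At a participation of 34% it is 1.96 × √(2 × 0.01 × 0.34 × 0.66 × 1.578 / 21) = ±3.6 points, and one could call it an unaddressed threat. It is not. It is part of the sampling error that the sample size already allows for through the ICC and CV, and the robust standard errors carry it into the intervals. Chance imbalance does not bias a randomised comparison.

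It is fair, too, that prior screening is not ignored (it has a pre-specified sensitivity analysis and a subgroup analysis), that allocation in one batch is inferred from the described sequence rather than stated, and that before randomisation the enriched lists sit with the practices and the register, not with the research team.

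What the objection does not answer is why a covariate collected in advance and already named in the plan should be kept out of the primary estimate. A sensitivity analysis does not improve the precision of the primary result, and it invites dispute if the two differ.

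**Conclusion.** The concern holds as a missed gain in precision and an inexact statement of the split. It is not an error that threatens validity or power.

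That the method does not guarantee 21:21:21 is certain; how often it misses depends on the assumed strata and blocks. The consequence for power is a few percentage points at most, in draws that are mostly rare.

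The more useful point is prior screening. Under the plan's own ICC and CV, about 81% of the variance lies between practices, so a practice-level predictor of participation is worth having. The size of the gain (7%, 20% or 39% of the variance) depends on a correlation that the protocol does not report. It would be smaller to the extent that state and remoteness, which are already adjusted for, explain the same variation. Practice size is a lesser matter, because its variation is already in the sample size.

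**What to change.** 1. Add prior screening to state and remoteness in the primary model, either as ever/never at patient level or as the practice's proportion with a prior kit return. Keep the strata-only model as the sensitivity analysis. This needs no new data. It does change the primary model, so it must be fixed before outcomes are seen. The adjusted odds ratio becomes conditional on prior screening, and the identity-link model carries one more term.

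2. Allocate all practices in one step. Give each arm an equal third of each stratum, rounded down, then distribute the leftover practices at random across strata so that every arm has 21. This needs only some programming by the randomising statistician. If random blocks are kept, describe 21:21:21 as a target.

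3. Optionally, draw at random from those allocations that also balance total eligible patients and the prior-return proportion. The statistician would need one coded row per practice before randomisation. That is a small extra data transfer, since the research team is otherwise due to receive de-identified data only at the end. The constraining variables must then be in the model.

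None of this needs more practices. According to Trial status, recruitment was complete and randomisation still lay ahead when the protocol was written.
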